## Abstract

**Background:**

Non-allergic rhinopathy (NAR), formerly known as vasomotor rhinitis, is a non-allergic and non-infectious chronic disease that is accompanied by nasal hyperemia, rhinorrhea, and no increase in the number of eosinophils. Although the medications for NAR, including intranasal corticosteroids and intranasal antihistamine, have been used in clinical practice, given the relative paucity of effective therapy with available medications, alternative non-pharmacologic treatments could play an important role in treating NAR. Acupuncture treatment is representative potential alternative therapy for the treatment of various diseases, including rhinitis. Therefore, the objective of this study was to evaluate the efficacy of pricking blood at Neiyingxiang (ExHN 9) relative to acupuncture treatment at Waiyingxiang (LI 20) in patients with NAR.

**Methods/Design:**

A randomized, parallel-group, controlled, assessor single-blinded, trial will be conducted. Fifty participants with NAR will be randomized into one of two groups: either the control group with acpuncture treatment at LI 20 or the experimental group with pricking blood at ExHN 9. After randomization, a total of three sessions of treatment will be performed once a week in both groups. The total nasal symptom score (TNSS) and the Mini-Rhinoconjunctivitis Quality-of-Life Questionnaire (MiniRQLQ) at baseline and the end of the trial will be used to evaluate the efficacy of each treatment.

**Discussion:**

This study will be the first randomized trial to evaluate the efficacy of pricking blood for the treatment of NAR. The results of this study will help establish an alternative approach for treating patients with NAR that do not respond to Western medication.

**Trial registration:**

The trial was registered with the Clinical Research Information Service (CRiS), Republic of Korea: KCT0000195.

## Background

Non-allergic rhinopathy (NAR), formerly known as vasomotor rhinitis, is a chronic non-infectious and non-allergic condition that displays the following symptoms: predominantly nasal congestion and rhinorrhea, which may be perennial, persistent, intermittent, or seasonal [1,2]. Unlike allergic rhinitis (AR), which is elicited by specific antigens, NAR is not relevant to allergen exposure and may be triggered by cold air, changes in climate or sexual hormone levels, strong smells, environmental tobacco smoke, pollutants, chemicals, exercise, or alcohol ingestion [1]. The exact prevalence of NAR has not been as well established as allergic rhinitis and one study suggested a relative prevalence rate of 76% for AR and 24% for non-allergic rhinitis, which corresponds to an approximate ratio of 3:1 [1,3].

The medications used for treating NAR have been studied less widely than those for AR [1]. The management of NAR consists of avoiding trigger factors in combination with medication, including intranasal corticosteroids, intranasal antihistamines, anti-cholinergics, decongestants, and nasal saline [1-5]. Even though patients with NAR are administered these medications, some patients do not adequately respond to them. For these patients, other agents can be considered such as capsaicin, botulinum toxin A, antileukotrienes, silver nitrate, or acupuncture [1,3]. However, given the relative paucity of good therapeutic agents with available medications, alternative non-pharmacologic therapies could play an important role in treating NAR.

Acupuncture has been used widely in East Asia and Europe for the treatment of various kinds of diseases, including rhinitis. In a systematic review that evaluated the clinical effectiveness of acupuncture for treating or preventing allergic rhinitis in 2009, acupuncture was found to be ineffective in the treatment of seasonal AR; however, acupuncture was shown to be effective for the treatment of perennial AR [6]. Recently, acupuncture treatment was shown to be effective in improving the symptoms of patients with persistent allergic rhinitis complicated by rhinosinusitis and asthma [7]. However, the majority of studies on acupuncture treatment have only examined AR and there were seldom randomized controlled trials. There has only been one randomized controlled pilot trial that showed a significant change in the nasal sickness score of patients with vasomotor rhinitis [8].

In Oriental medicine, Waiyingxiang (LI 20) is generally used in clinical practice to treat local diseases of the nose including rhinitis, sinusitis, and olfactory disorders [7-12]. Neiyingxiang (ExHN 9) is located at the junction between the mucosa of the alar cartilage of the nose and the nasal concha in the nostril and is commonly used for olfactory disorders, chronic rhinitis, sequela of Bell's palsy, and headache [13-15].

Therefore, we will conduct a randomized controlled pilot trial to assess the efficacy of pricking blood at ExHN 9 relative to acupuncture treatment at the LI 20 in patients with NAR.

## Method/Design

### Objective

The current randomized, assessor single-blinded, parallel-group, single-center study was designed to evaluate the clinical efficacy of pricking blood at ExHN 9 for the treatment of NAR relative to the control group, which involved administration of acupuncture treatment at LI 20.

### Design

This study will be a randomized, real acupuncture-controlled, assessor single-blinded and single-center pilot trial. The study will be conducted in the following order: enrollment after screening via inclusion and exclusion criteria, randomization, a treatment period of 3 weeks, and assessment (Figure 1).

**Figure 1 F1:**
[figure not shown]
**Flow chart of the study**.

### Participants and eligibility

#### Inclusion criteria

Eligible for inclusion in this study will be patients ≥ 8 years of age with a diagnosis of NAR and at least a 3-month history of continuous nasal symptoms related to defined triggers (for example, changes in temperature and/or humidity, strong odors, and airborne irritants). Patients must have had a history of negative results in allergic tests (MAST test, serum IgE) and an eosinophil count within a normal range.

#### Exclusion criteria

Patients that had a history of nasal surgery, nasal polyp, psychiatric disorders, drug addiction, and autoimmune disease will be excluded, as well as patients that could not be subjected to acupuncture treatment, such as individuals that were pregnant or had a blood clotting disorder. Participants will be ineligible if they have undergone acupuncture treatment or Western medical treatment for rhinitis within 1 month of taking cold medicine, within 2 weeks prior to registration, or if cold medicine was taken during the trial. Patients who were treated with gastritis, gastric ulcer (using H2 blocker antiacid), who had plans to participate in another clinical trial during this clinical trial, who participated in another clinical trial within 6 months, or who are not willing to not comply with the protocol of this study protocol will also be excluded. Within 3 weeks after enrollment in this trial, no concomitant therapy will be permitted.

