#### Randomization and blinding

After enrollment, participants will be randomly assigned to control and experimental groups. The allocation ratio will be 1:1. Randomization will be performed at a site remote from trial location. Random numbers will be generated using a computerized random-number generator through the block-randomization method (Excel, Microsoft Office 2007) for sequence generation. Two separate databases will be generated: a 'patient' database, which lists basic information, such as the patient name, contact details, and so on, and a 'randomization' database, which contained data on patients that have been registered in the trial along with their allocations. The 'patients' database will be accessible to any researcher whereas the 'randomization' database will be password-protected so that it will be accessible only by the principal investigator and a nominated statistician [16]. The assessor, who will not be the acupuncture practitioner, and who will be blinded to the allocation results until the end of study, will assess the outcome of treatment.

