### Statistical methods

#### Statistical analysis plan

Statistical analysis will be conducted on an intention-to-treat basis with a 95% confidence interval using SPSS version 12.0 for Windows. Missing values for patients that drop out of the study will be analyzed using the last observation carried forward (LOCF) method. Data will be displayed as the mean ± standard deviation (SD) for continuous data or *n *(%) for categorical data. To control for baseline differences between groups, variables that are significantly different at baseline will serve as covariates in the analyses.

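### In-trial cold-medicine use is listed as a ground for ineligibility, so randomised patients are either removed against intention-to-treat or given zero TNSS change by LOCF

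*Protocol article*

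**What the plan says.** All references are to the protocol article.

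- **Exclusion criteria.** The sentence begins "Participants will be ineligible if they have undergone acupuncture treatment or Western medical treatment for rhinitis" and continues "within 1 month of taking cold medicine, within 2 weeks prior to registration, or if cold medicine was taken during the trial". The same section ends with a conduct rule, "Within 3 weeks after enrollment in this trial, no concomitant therapy will be permitted", and attaches no consequence for the analysis.
- **Design.** The order of steps is "enrollment after screening via inclusion and exclusion criteria, randomization, a treatment period of 3 weeks, and assessment".
- **Randomization and blinding.** "After enrollment, participants will be randomly assigned to control and experimental groups". The assessor is the only person described as blinded.
- **Primary outcome.** TNSS sums rhinorrhea, sneezing, nasal itching and nasal obstruction, each scored 0 to 3. The patient records it at baseline and at the end of the trial.
- **Statistical analysis plan.** "Statistical analysis will be conducted on an intention-to-treat basis with a 95% confidence interval". For drop-outs, "Missing values for patients that drop out of the study will be analyzed using the last observation carried forward (LOCF) method".
- **Sample size.** 50 patients, 25 per group, with an assumed drop-out rate of 20%.

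**The concern.** An eligibility criterion has to be decidable before randomisation. This one depends on something the patient does during the 3 weeks of treatment. The article does not say whether such a patient leaves the analysis, leaves the study, or stays in both, and it nowhere separates stopping participation from removal from the analysis.

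This matters because the event may not be neutral. The symptoms of a cold are largely those that TNSS scores, and patients, who rate their own symptoms, are not described as blinded. Whoever drops out under this rule may therefore be selected on outcome, and the selection may differ between arms. The Discussion makes a positive pilot result the trigger for a large trial, so a distorted contrast would feed into that decision.

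The same sentence also runs the washout windows together. As punctuated, the 1-month window is counted from taking cold medicine, and the 2-week window has no clear object.

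**Working it through.** **1. Order of events.** Screening and enrolment come first, then randomisation, treatment and assessment. No run-in is described. The in-trial clause can therefore be met only after enrolment and, for practical purposes, after allocation.

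**2. The two readings.**
- *Removed from the analysis.* The analysed set falls below the 50 randomised by an unknown number. That is not intention-to-treat.
- *Withdrawn and handled as a drop-out.* The patient stays in the set. The last TNSS before the end of trial is the baseline value, so the imputed change is baseline minus baseline = 0, and an end-of-trial score that could have been collected is not used.

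**3. Size under a common mechanism.** The article gives no rate of cold-medicine use and no SD for TNSS change, so there is no stated figure to reproduce. Assumed inputs: SD of change 2.5; mean control change -2; probability of removal rising with a worse change, by the same curve in both arms; overall removal of 5%, 10% or 20%. The top of that range equals the planned drop-out rate. Simulated differences, experimental minus control (negative favours experimental):

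| True difference | Overall removal | Removed: control / experimental | Excluded | Withdrawn, LOCF |
|---|---|---|---|---|
| 0 | 5%, 10%, 20% | equal | about 0 | about 0 |
| -1.0 | 5% | 6.6% / 3.4% | -0.88 | -0.92 |
| -1.0 | 10% | 12.8% / 7.3% | -0.81 | -0.89 |
| -1.0 | 20% | 24.5% / 15.4% | -0.71 | -0.86 |
| -1.5 | 5% | 7.3% / 2.7% | -1.32 | -1.39 |
| -1.5 | 10% | 14.1% / 5.9% | -1.24 | -1.37 |
| -1.5 | 20% | 26.7% / 13.3% | -1.09 | -1.34 |

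So there is no bias under the null, and attenuation when a true difference exists.

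**4. Size if use differs by arm, with exclusion.** Take no true difference and remove the worst fraction q of an arm. The remaining mean, in SD units, is -φ(z)/(1-q), where z cuts off the worst fraction q.
- q = 0.20: -0.350
- q = 0.12: -0.227
- q = 0.04: -0.090

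Removing 20% against 4% gives a spurious 0.350 - 0.090 = 0.26 SD; 12% against 4% gives 0.14 SD. Both favour the arm with more use. For scale, the 95% CI half-width at 25 per arm is 2.01 × √(2/25) = 0.57 SD.

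**5. Size under LOCF if use is unrelated to outcome** (for example, a chance cold). Each arm's mean change is multiplied by (1 - w), where w is the fraction withdrawn.
- w = 10% in both arms: -1.5 × 0.90 = -1.35.
- 20% against 4%, no true difference, mean change -2 in both arms: -2 × 0.80 = -1.60 against -2 × 0.96 = -1.92. The gap is 0.32 points, or 0.32/2.5 = 0.13 SD, and it counts *against* the arm with more use.

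Steps 4 and 5 point in opposite directions, so the sign cannot be settled from the article.

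**6. Washout wording.** Read literally, the 1-month limit on rhinitis treatment starts from cold-medicine use and not from registration. Read as a list, rhinitis treatment within 2 weeks before registration also excludes. Read with a misplaced comma, the sentence holds two separate windows for two types of treatment. The text does not settle which is meant.

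**The case against.** The strongest reply is that the article never says a randomised patient's data are deleted. It says ineligible, and it states its analysis rule separately. If taking cold medicine ends participation, the patient becomes a drop-out, LOCF applies, and both sections can be followed. A condensed article may also leave withdrawal rules to the full protocol. This stands to the extent that a flat contradiction with intention-to-treat is a reading a reader might infer but the text does not force. It does not clear the clause. The article states a rule, places it under eligibility, and on the kinder reading that rule sets the primary outcome of these patients to zero change.

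Three other stronger inferences are tempting and not supported:

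- *That patients are removed because of their nasal symptoms.* The article does not say why cold medicine would be taken, and an unrelated cold is possible. Overlap with the TNSS items makes a link to outcome plausible, no more.
- *That the rule flatters the new treatment.* The 0.26 and 0.14 SD figures are arithmetically right, but they assume markedly different use by arm with no true difference, and removal of exactly the worst patients. Nothing in the article indicates such ratios. A common mechanism gives attenuation or no bias.
- *That recently treated patients will be admitted.* This depends on one parsing of a badly punctuated sentence.

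It is also fair that this is a 50-patient pilot, described in its Discussion as unable to be conclusive, and that even 0.26 SD is less than half the CI half-width.

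**Conclusion.** The point holds in a limited form. In-trial cold-medicine use cannot be an eligibility criterion. As written, it leaves two possible treatments of the same patient: removal, which conflicts with the intention-to-treat statement, or withdrawal, which makes the change in TNSS exactly zero. Either can alter the primary comparison.

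Size and direction are unknown because no rate of use is given. With a common symptom-related mechanism there is no bias under the null and attenuation otherwise: a true -1.5 points becomes -1.32 to -1.09 with exclusion, or -1.39 to -1.34 with LOCF, at 5% to 20% removal. If use differs by arm, bias can go either way. These figures rest on the assumed SD, control change and removal curve. The conclusion does not: it rests on the order of events and the stated analysis rules. Should-fix, with the washout wording as a secondary repair.

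**What to change.** 1. Take in-trial cold-medicine use out of the eligibility criteria.
2. Reconcile the Exclusion criteria with the Statistical analysis plan by stating that every randomised patient is followed to the end-of-trial TNSS and analysed as randomised, whether or not cold medicine was taken.
3. Record cold-medicine use as a protocol deviation, and examine its influence in a sensitivity analysis, for example one that treats scores after its use as missing.
4. Rewrite the washout sentence so that the 1-month and 2-week windows each name what they apply to and are anchored to registration, as the sponsor intends.

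Whether cold medicine is permitted during the trial, or ends study treatment, is for the sponsor to state.

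The cost is a few sentences of wording, some extra follow-up of patients who would otherwise have left, and one added analysis. The Trial status section says recruitment has not begun, so no collected data are affected. The small downside is that some effect of off-protocol medication stays in the primary estimate; the sensitivity analysis shows how much that matters.

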#### Recruitment

Participants will be recruited via an internet advertisement posted on the website of the Kyung Hee Medical Center and via ad-posters.

#### Randomization and blinding

After enrollment, participants will be randomly assigned to control and experimental groups. The allocation ratio will be 1:1. Randomization will be performed at a site remote from trial location. Random numbers will be generated using a computerized random-number generator through the block-randomization method (Excel, Microsoft Office 2007) for sequence generation. Two separate databases will be generated: a 'patient' database, which lists basic information, such as the patient name, contact details, and so on, and a 'randomization' database, which contained data on patients that have been registered in the trial along with their allocations. The 'patients' database will be accessible to any researcher whereas the 'randomization' database will be password-protected so that it will be accessible only by the principal investigator and a nominated statistician [16]. The assessor, who will not be the acupuncture practitioner, and who will be blinded to the allocation results until the end of study, will assess the outcome of treatment.

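### The principal investigator's access to the running allocations of a single-centre, block-randomised trial puts allocation concealment at risk

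*Protocol article*

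**What the plan says.** All the rules on allocation are in the protocol article under Randomization and blinding.

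- Timing and ratio: "After enrollment, participants will be randomly assigned to control and experimental groups", and "The allocation ratio will be 1:1".
- Place: "Randomization will be performed at a site remote from trial location".
- Method: "Random numbers will be generated using a computerized random-number generator through the block-randomization method". The block size is not given, nor whether it is fixed or varied.
- Records: there are two databases. Any researcher may open the one with patient details. The other "contained data on patients that have been registered in the trial along with their allocations" and is "password-protected so that it will be accessible only by the principal investigator and a nominated statistician".

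Under Design the study is a "real acupuncture-controlled, assessor single-blinded and single-center pilot trial". The assessor is someone other than the practitioner and stays blinded to the end of the study. Under Primary outcome, patients score their own nasal symptoms (TNSS). Sample size gives 50 patients, 25 per group, and Trial status says that recruitment has not begun.

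**The concern.** Remote randomisation hides the next assignment only from people who cannot work it out. In a permuted block, the assignments already made show how many of each arm are left, so the future list need not be visible. With one centre there is a single stream of patients and, as far as the article says, a single sequence to follow. The article withholds the allocation database from other researchers, so it treats the content as sensitive, yet it opens it to the head of the trial and does not keep that role away from screening or enrolment.

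Someone who sees the allocations and also influences entry could bring forward, delay or decline a borderline patient according to the likely next arm. Entry leaves room for this: the inclusion criteria rest on a diagnosis and a history of at least three months of symptoms with no minimum TNSS, and willingness to comply is a matter of judgement. The primary outcome is change in TNSS, which depends on severity at baseline, so uneven steering of severe cases would shift the comparison.

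Assessor blinding does not help here. It acts after allocation, and it gives this primary outcome little protection anyway: practitioners know what they give, and patients who score themselves can in effect tell an intranasal prick from needles at LI 20 with 15 minutes lying down.

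**Working it through.** **Inputs from the article.** Blocks, 1:1 ratio, one centre, allocations of registered patients visible to the principal investigator, 50 patients. The article gives no figure for predictability, so there is none to reproduce.

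**Assumptions.** The block size b = 2k is fixed and known to the person guessing, who sees every earlier allocation. As b is not stated, a range is shown.

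**Step 1: assignments known with certainty.** These are the ones left once one arm has been used up within a block. Their expected number per block is 2k/(k+1), so the share is [2k/(k+1)]/b = 1/(k+1).

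Check by hand for b = 4: the third place is certain in 2 of the 6 possible sequences (the first two alike), and the fourth place always. That gives 1 + 1/3 = 4/3 per block, and (4/3)/4 = 1/3.

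**Step 2: best-guess success.** The guesser always names the arm with more places left and tosses a coin at a tie. The expected share correct is [k + (4^k/C(2k,k) − 1)/2]/b. For b = 4: [2 + (16/6 − 1)/2]/4 = 2.833/4 = 70.8%.

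| Block size | Certain | Guessed correctly | Certain out of 50 |
|---|---|---|---|
| 2 | 50% | 75% | 25 |
| 4 | 33.3% | 70.8% | about 17 |
| 6 | 25% | 68.3% | 12 to 13 |
| 8 | 20% | 66.6% | 10 |
| 10 | 16.7% | 65.3% | about 8 |
| 50 (one block) | 3.8% | 57.9% | about 2 |
| Full concealment | 0% | 50% | 0 |

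The rows for blocks of 2 to 10 were confirmed by listing every possible block. The last column is the share times 50 and ignores an incomplete final block. All figures fall if the size is unknown to the guesser or varies.

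**Step 3: would the planned analysis catch steering?** Under Statistical analysis plan, only variables that differ significantly at baseline become covariates. With 25 per arm, a t-test reaches p < 0.05 only when the observed baseline difference exceeds about 2.01 × √(2/25) = 0.57 SD. A smaller imbalance would go unadjusted, and unmeasured differences cannot be adjusted for at all.

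**The case against.** The strongest reply is that the article describes a sound arrangement and that the mechanism needs facts it does not contain.

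- *No section says that the principal investigator screens, confirms eligibility or enrols.* This stands. Recruitment mentions only advertisements, and treatment is given by practitioners. The risk is conditional on that role having a part in entry, but nothing excludes it.
- *Randomisation is remote and follows enrolment, and the database is described as holding patients already registered.* This stands too. A reader might infer that concealment is lost, or that the future sequence is open to the principal investigator. The text supports neither. The safeguards still do not stop prediction from past allocations.
- *The block size may be in the full protocol.* This is fair, and its absence is not the point. The access rule is stated outright and needs changing whatever the size. The percentages remain conditional on the size being fixed and known.
- *The trial is not unblinded.* Correct: it has a blinded assessor. Only practitioners and, in effect, patients know the treatment.
- *Withdrawing one password is not enough, because practitioners at one centre see the treatments being given.* This stands, and is why the fix also varies the block size.
- *It is a pilot that claims no conclusive result.* True, but the Discussion makes a larger trial depend on positive results, so bias here would still mislead.

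A reader might also infer that the nominated statistician, with the same access, will make the data-dependent choices of covariates and tests. The article does not say who does the analysis, so that is not part of this point.

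**Conclusion.** The point holds as a risk to concealment and should be dealt with before recruitment opens. The article expressly lets the principal investigator of a single-centre, 1:1 block-randomised trial see the running allocations, and does not bar that role from screening or enrolling.

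For a known fixed block of 2 to 10, between 50% and 17% of assignments would be certain, and 75% to 65% guessed correctly against 50% under concealment. A single block of 50 gives about 4% and 58%. These figures assume complete sight of earlier allocations and knowledge of the block size. They measure how predictable the assignments would be. They do not measure bias, and the article gives no ground for saying that patients would in fact be selected.

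**What to change.** 1. Restrict the randomisation database to the remote randomisation site or the nominated statistician until database lock, so that no one who screens or enrols, including the principal investigator, can see it.
2. Generate the list with randomly varying block sizes that are not disclosed to site staff. This also limits prediction from the treatments that practitioners see given.
3. Release each assignment only after the patient's eligibility and consent have been logged.

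The cost is a permissions change and a regenerated list, both simple while the trial is not yet recruiting. The final split may be a patient or two off 25:25. Figures of 0% certain and 50% guessed would be reached only if nobody who enrols can learn earlier allocations by any route. In an open single-centre trial the first step alone does not guarantee that, so the first two belong together.
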